#### Concealment mechanism {16b}

Allocation concealment will be ensured as it will not be possible to conduct the computer-generated randomisation until the baseline assessment is completed for each participant.

#### Implementation {16c}

An external collaborator (Zitelab Aps, http://www.zitelab.dk/) will generate the allocation sequence. This collaborator is not involved in outcome assessments or the CBT-i intervention. [name] will enrol participants and, immediately after randomisation, inform them to which group they have been allocated.

### Assignment of interventions: blinding

#### Who will be blinded {17a}

Outcome assessments are conducted by project nurses specialising in rheumatology, medical laboratory technologists or neurophysiology assistants, all of whom will be blinded to participant allocation.

Application of PSG equipment and instructions on how to use the actigraph and subsequent analysis of data will be conducted by neurophysiology assistants at the DCSM. Patient-reported outcome measures will be collected via questionnaires on tablets handed out by a project nurse. To assess the outcome of disease activity, a project nurse will examine the joints of participants to identify the number of swollen and tender joints related to DAS28. Blood samples will be taken and analysed by a medical laboratory technologist.

[name] will conduct the CBT-i intervention and is therefore not blinded to participant allocation.

#### Procedure for unblinding if needed {17b}

The trial design is open-label with only the outcome assessors being blinded so unblinding will not occur.

### Data collection and management

#### Plans for assessment and collection of outcomes {18a}

Data will be collected from PSG, actigraphy, physical examination, blood samples, a medical journal and questionnaires as presented in Table 2 and as follows.

The data collected from PSG cover SE, SOL, WASO, TST, sleep stages, number of awakenings, apnoea-hypopnoea index and leg movements. The data collected from actigraphy cover SE, SOL, WASO and TST for 7 continuous nights. From the medical journal we will collect data on duration of RA, anti-rheumatic drugs and glucocorticoids. Questionnaires will provide data on patient-reported SE, SOL, WASO, TST, insomnia, sleep quality, fatigue, impact of RA, depressive symptoms, pain, functional status, HRQoL, patient global assessment, physician global assessment, sociodemographic information, lifestyle, RA-related information, comorbidity, duration of insomnia, antidepressant drugs and hypnotic drugs. From the physical examination we will obtain data on swollen joints and tender joints counts (of 28 examined joints), and we will collect data on CRP from serum samples.

#### Plans to promote participant retention and complete follow-up {18b}

Dates for assessments will be planned by [name] together with each participant, and all participants will receive a text reminder on their telephone or an email the day before a scheduled assessment. If participants withdraw consent for follow-up assessment of one outcome, they will be given the option to continue with assessments for other outcomes.

#### Data management {19}

All participants will receive an identification code and all data will be de-identified.

A list of identifiable participant information associated with each identification code will be stored electronically separately from the research data for 5 years. Patient-reported information will be completed electronically on a tablet, which will be used only for participants in this trial and is linked to the DANBIO Reuma electronic case report form.

#### Confidentiality {27}

All information collected during the trial will be kept confidential in accordance with Danish Data Protection Agency rules. All data will be processed confidentially according to the Act on Processing of Personal Data.

#### Plans for collection, laboratory evaluation and storage of biological specimens for genetic or molecular analysis in this trial/future use {33}

There will be no biological specimens collected for genetic or molecular analysis in this trial.

### Statistical methods

#### Statistical methods for primary and secondary outcomes {20a}

All main analyses will be conducted based on the intention-to-treat (ITT) population. We plan to conduct both an analysis of the full analysis set (patients with outcome data available at baseline) and a per-protocol analysis so that any differences between them can be explicitly discussed and interpreted. The ITT principle states the effect of a treatment policy (i.e. the planned treatment regimen) rather than the actual treatment given. The consequence of conducting ITT analyses is that participants allocated to a treatment group should be followed up, assessed and analysed as members of that group, irrespective of their compliance to the planned course of treatment. Robustness is a concept that refers to the sensitivity of the overall conclusions to various limitations of the data, assumptions and analytic approaches to data analysis. Robustness implies that the treatment effect and primary conclusions of the trial are not substantially affected when analyses are carried out based on alternative assumptions or analytical approaches.

We will control the α level across only the most important hypotheses by use of a hierarchical testing strategy to preserve a type 1 error rate of 5% for the primary outcome of change in SE assessed after treatment at week 7, followed by SE assessed at follow-up after 26 weeks. All the patient-reported outcome measures and other secondary outcome measures will, by principle, only be clinically relevant after 26 weeks. The sleep-related key secondary outcomes (SOL, WASO, TST, insomnia and sleep quality) will only be considered statistically significant with a *P* value <0.01 (0.05/5). The RA-related key secondary outcomes (fatigue, impact of RA and depressive symptoms) will only be considered statistically significant with a *P* value <0.017 (0.05/3) as described in Fig. 2.

In the Sleep-RA trial with repeated measures, participants will be randomly assigned to treatment groups, and outcome observations are made at two time points on each patient. We anticipate that measures on the same patient at different times are correlated and that measures taken close together in time will be more highly correlated than measures taken further apart in time; observations on different patients will be assumed to be independent.

Data will be analysed using the PROC MIXED procedure of the statistical program SAS System, with baseline level as a covariable, using a multilevel repeated-measures random-effects model, with participants as the random effect factor and based on a restricted maximum likelihood estimate. For the primary outcome measure, the after-treatment value will be the response variable, and the baseline values of treatment group (two levels), stratum (i.e. two levels according to the randomisation) and time (two levels) will be the covariates. Assessment of these baseline values (main effects) will be of interest, along with the interaction between treatment group and time. This statistical model holds all between-group comparisons at both assessment points and allows for evaluation of the average effect over the period from baseline to follow-up at 26 weeks.

The SAS statistical package (v.9.4; SAS institute Inc., Cary, NC, USA) and R 3.0.1 (http://www.R-project.org, the R Foundation for Statistical Computing) will be used for the statistical models.

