### Objectives {7}

Our primary objective is to compare the effect of CBT-i relative to usual care on changes in SE from baseline to week 7 in patients with RA.

Our key secondary objectives are to compare the effect of CBT-i relative to usual care on changes in sleep onset latency (SOL), wake after sleep onset (WASO), total sleep time (TST), insomnia, sleep quality, fatigue, impact of RA and depressive symptoms from baseline to week 26 in patients with RA.

Other secondary objectives are to compare the effect of CBT-i relative to usual care on changes in SE, SOL, WASO, TST, insomnia, sleep quality, fatigue, impact of RA, depressive symptoms, disease activity, tender joints, swollen joints, acute-phase reactant value, patient global assessment, physician global assessment, pain, functional status and HRQoL from baseline to weeks 7 and 26 in patients with RA.

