#### Key secondary outcomes

We will examine the effect of improved sleep on key sleep outcomes and key RA outcomes at follow-up at week 26 if CBT-i has a significant positive effect on the primary outcome of SE after treatment at week 7, as presented in Fig. 2.

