##### Key sleep outcomes

SOL will be assessed with PSG. SOL is the amount of time it takes to go from being fully awake to being asleep [70].

WASO will be assessed with PSG. WASO is the cumulative time awake between sleep onset and the final morning awakening [70].

TST will be assessed with PSG. TST is the cumulative time asleep between sleep onset and the final morning awakening [70].

Insomnia will be assessed with the Insomnia Severity Index questionnaire. This is a seven-item questionnaire designed to evaluate insomnia severity based on difficulties falling asleep, night-time awakenings, early morning awakenings, impairment of daytime functioning due to sleep problems, noticeability of impairments, distress or worry caused by sleep difficulties and dissatisfaction with sleep over the past 2 weeks. Each item is rated using a five-point Likert scale ranging from 0 (not at all) to 4 (very much), for a total score ranging from 0 (no insomnia) to 28 (clinical insomnia) [71]. A cut-off of 11 has been validated in a clinical sample of people with insomnia and demonstrated a sensitivity of 97.2% and a specificity of 100% [56].

Sleep quality will be assessed with the Pittsburgh Sleep Quality Index (PSQI) questionnaire. The PSQI measures self-reported sleep over the past 4 weeks [72]. It includes nine items/18 questions with seven categories, including subjective sleep quality, sleep latency, sleep duration, habitual SE, sleep disturbances, use of sleep medications and daytime dysfunction. A global sum score for the PSQI >5 indicates poor sleep. The Cronbach’s α value for the PSQI is 0.83 [73].

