#### Other secondary outcomes

We will examine other secondary outcomes after treatment at week 7 and at follow-up at week 26 if CBT-i has a significant positive effect on the primary outcome of SE after treatment at week 7.

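### The prose does not agree on whether week-26 sleep efficiency stands between the primary test and the eight key secondary outcomes

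*Protocol article*

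**What the plan says.** **Statistical methods for primary and secondary outcomes {20a}.** Alpha is to be controlled across only the most important hypotheses, "by use of a hierarchical testing strategy to preserve a type 1 error rate of 5" per cent. The sequence given is "the primary outcome of change in SE assessed after treatment at week 7, followed by SE assessed at follow-up after 26 weeks". The section then sets thresholds for two families of key secondaries: P < 0.01 (0.05/5) for the five sleep outcomes and P < 0.017 (0.05/3) for the three RA outcomes. It refers to Fig. 2.

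**Key secondary outcomes.** The week-26 key outcomes will be examined "if CBT-i has a significant positive effect on the primary outcome of SE after treatment at week 7, as presented in Fig. 2". No condition on week-26 SE is stated.

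**Other secondary outcomes.** The same week-7 SE condition applies here: "We will examine other secondary outcomes after treatment at week 7 and at follow-up at week 26 if CBT-i has a significant positive effect".

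**Objectives {7}.** The key secondary objectives cover "changes in sleep onset latency (SOL), wake after sleep onset (WASO), total sleep time (TST), insomnia, sleep quality, fatigue, impact of RA and depressive symptoms", all to week 26. SE is not among them. SE does appear under the other secondary objectives, at weeks 7 and 26, with no instrument named.

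**Key sleep outcomes and Other sleep outcomes.** The key list begins at sleep onset latency ("SOL will be assessed with PSG") and has no entry for SE. The other list has SE by actigraphy and by the PSQI questionnaire. PSG-measured SE at week 26 therefore has no explicit entry in either outcome list.

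**The concern.** A hierarchical procedure protects the type I error rate only if its order is fixed before the results are known. Here the statistical section gives week-26 SE a place in the order, while the outcomes section describes a route to the key secondaries that does not pass through it.

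If SE is significant at week 7 but not at week 26, a fixed sequence built on the first section would stop. The rule in the second section would go on to test all eight key secondaries. The same data could then support a confirmatory claim on insomnia severity or fatigue, for example, or leave it descriptive. Fading of a behavioural effect over the 19 weeks between the two assessments is plausible enough for the case to need a rule.

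**Working it through.** **1. Reproduce the plan's own figures.** Inputs from Sample size {14}: difference 6 points, SD 7.5, two-sided 0.05, pooled t test, 30 per arm (26 per arm after attrition).

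- Standard error of the difference = 7.5 × √(2/n): 1.936 for n = 30 and 2.080 for n = 26.
- Noncentrality = 6 / standard error: 3.098 and 2.884. Critical t: 2.002 (58 df) and 2.009 (50 df).
- Noncentral-t power: 86.1% and 80.7%, as stated in the protocol.

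**2. Find where the readings part.**

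| SE week 7 | SE week 26 | Fixed sequence from the statistical section | Key secondary outcomes section |
|---|---|---|---|
| not significant | either | closed | closed |
| significant | significant | open | open |
| significant | not significant | closed | open |

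Only the last row matters.

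**3. Probability of the last row.** Treat the two test statistics as bivariate normal with unit variances, correlation ρ and means 3.098 (week 7) and d/1.936 (week 26), where d is the true week-26 difference. With c = 2.002:

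P(readings differ) = P(Z7 > c) − P(Z7 > c and Z26 > c)

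P(Z7 > c) = Φ(3.098 − 2.002) = 0.864, within 0.3 points of the exact 86.1%. Three inputs are not in the protocol and are assumed: d from 0 to 6 points, ρ from 0.3 to 0.7, and the same SD of 7.5 at both visits.

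| d, 30 per arm | ρ = 0.3 | ρ = 0.5 | ρ = 0.7 |
|---|---|---|---|
| 6 (fully kept) | 0.864 − 0.763 = 10.1% | 0.864 − 0.778 = 8.6% | 6.7% |
| 4 | 38% | 37% | 35% |
| 3 (halved) | 56% | 55% | 54% |
| 0 (gone) | 84% | 84% | 84% |

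With 26 per arm, the fully kept case gives 8–13% and the halved case 53–55%. Using 1.96 instead of the t critical value moves the 30-per-arm figures to 6–10% and 53–55%, so the approximation is not what drives the result.

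**4. The two families.** Sleep: 5 × 0.01 = 0.05. RA: 3 × 0.05/3 = 0.05. Opened in parallel with all eight nulls true, the bound on the error rate is 0.05 + 0.05 = 0.10. If the tests are independent it is 1 − 0.99⁵ × (1 − 0.05/3)³ = 0.096. Settling the gate alone would therefore not give 5% control across the key secondaries.

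**The case against.** **Fig. 2.** Both sections refer to this figure, which is captioned as the statistical method for the key secondary outcomes and is not reproduced in the text reviewed. It may fix the order in advance. This stands: it cannot be said that the order is truly open, only that the prose sections do not match and that at least one must be brought into line with the figure.

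**No blocking rule in words.** A reader might infer that the statistical section forbids all key secondary testing after a failed week-26 SE test. It does not say so. It names a two-step SE sequence and then gives the families their own thresholds, so the families could be opened by week-7 SE as the outcomes section says. Blocking is the ordinary meaning of a hierarchy but remains an inference. Even on the milder reading, the part that week-26 SE plays is left undefined.

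**A third, exploratory role.** A reader might infer that the objectives demote week-26 SE to the lowest tier. The documents do not establish this. The SE listed there may be the actigraphy and PSQI measures described under Other sleep outcomes; latency, wake time and total sleep time also appear in both tiers, which fits a difference of instrument. What is established is an omission from the key lists.

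**Week-7 secondary analyses.** A reader might also see a contradiction in analysing secondary outcomes at week 7 when the statistical section calls them clinically relevant only after 26 weeks. That remark concerns interpretation and does not forbid a week-7 analysis.

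**Reach.** The primary test, sample size and randomisation are untouched, and the sample size section itself calls the week-26 secondary analyses exploratory. This limits the severity. It does not remove the need for one stated order, since the protocol sets formal significance thresholds for these outcomes.

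**Conclusion.** The point holds as an unreconciled decision rule. The statistical section ranks week-26 SE second, the outcomes section opens the key secondaries without it, and the key lists omit it.

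The readings diverge in about 7–10% of trials if the 6-point effect is fully kept and in about 54–56% if it halves, under the assumptions in step 3. In those trials only key secondaries that also reach P < 0.01 or P < 0.017 are affected; for these, the section followed decides whether the claim is confirmatory.

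The fixed-sequence reading is natural but not explicit, and Fig. 2 may resolve it. Hence: should fix, moderate confidence.

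**What to change.** Before database lock, write one sequence and make the Objectives, Key secondary outcomes, Key sleep outcomes and statistical methods sections agree with it and with Fig. 2. Either of two versions works:

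1. List PSG-measured SE at week 26 as the first key secondary outcome, and make its significance, after week-7 SE, the condition that opens the other key secondaries. The cost is that fewer trials reach them: about 7–10% fewer if the effect is kept, more if it fades.
2. Keep week-7 SE as the only gate, and state in the statistical methods section that week-26 SE does not gate the key secondaries. The cost is that they may be claimed when the SE benefit is not confirmed at the same visit.

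In either version, state whether the two families fall under the 5% control. If they do, add a rule that shares or orders the alpha between them, at some cost in power. If each family is meant to carry its own 5%, say so.

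The work is wording in four sections, a check of Fig. 2 and a registry update. No data collection changes.

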### Intervention description {11a}

In the Sleep-RA trial, CBT-i is a 6-week intervention with participant attendance of 2 h per week. The intervention will be conducted in groups of two to six participants per group. All sessions will be conducted by [name], who is a trained nurse in CBT-i.

The manual for the CBT-i intervention in Sleep-RA has been developed by [name], [name] and [name] in collaboration with a clinical psychologist trained in CBT-i and patient research partners, in accordance with the “Template for Intervention Description and Replication” checklist and guide [58]. The manual is guided by theory on CBT-i, available evidence and previous CBT-i manuals [54, 59–66]. The CBT-i intervention consists of sleep education, stimulus control, sleep restriction, cognitive therapy and relaxation, as presented in Table 1. The CBT-i intervention includes presentations by [name], exchanges of experiences, assignments, relaxation exercises and individual and shared discussions and reflections on how to use the knowledge gained during the intervention and changed habits related to sleep in daily life.

**Table 1 Tab1:** Cognitive behavioural therapy for insomnia: intervention overview

**Session 1**	Introduction	Presentation
		Goals
		Expectations
	Sleep education	Normal sleep and its determinants
		Sleep needs
		Consequences of insomnia
		Nature of insomnia
		Evaluation of participant sleep
		Sleep hygiene
	Sleep restriction	Introduce sleep diary
**Session 2**	Follow-up	Since last session
	Sleep education	Sleep hygiene
	Stimuli control	Rationale; conditioned arousal
		Instructions
	Sleep restriction	Rationale; sleep drive and sleep consolidation
		Sleep efficiency and sleep window for week 2
	Relaxation	Bed time wind-down
**Session 3**	Follow-up	Since last session
	Stimuli control	Experiences and challenges
	Sleep restriction	Experiences and challenges
		Sleep efficiency and sleep window for week 3
	Cognitive therapy	Cognitions affecting sleep
		Cognitive techniques to treat insomnia
**Session 4**	Follow-up	Since last session
	Sleep restriction	Experiences and challenges
		Sleep efficiency and sleep window for week 4
	Cognitive therapy	Experiences and challenges
		Cognitive techniques to treat insomnia
		Worry-time
	Relaxation	Rationale, break the tension and return to a relaxed state
		Body scan meditation
**Session 5**	Follow-up	Since last session
	Stimuli control	Experiences and challenges
	Sleep restriction	Experiences and challenges

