### Sample size {14}

With a total sample size of 60 patients with RA (30 allocated to CBT-i as treatment and 30 allocated to usual care), we will have more than 85% power to detect a group difference in the primary outcome of average SE assessed by PSG after treatment at week 7 and subsequently with reasonable power in the key secondary outcome assessed at follow-up at week 26.

For a two-sample pooled *t* test of a normal mean difference with a two-sided significance level of 0.05 (*P* < 0.05), assuming a common standard deviation of 7.5% in SE, a total sample size of 60 with allocation ratio of 1:1 has a power of 86.1% to detect a mean difference of 6 percentage points in SE.

The Sleep-RA trial is sufficiently powered to detect the anticipated difference with a total sample size of 52 participants. Assuming a balanced attrition rate (no more than four withdrawals per group) we will obtain enough statistical power (80.7%, i.e. >80%) to detect a mean difference of 6 percentage points in SE.

With a total sample size of 60 patients and assuming a balanced design (1:1), exploratory analyses of any of the secondary outcomes collected at week 26 will have enough statistical power (>80%) to detect a standardised mean difference of 0.80 (i.e. a Cohen’s effect size corresponding to a large clinical effect).

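### CBT-i is delivered in therapy groups but the plan assumes independent patients; if the within-group correlation is positive, the standard error is too small and the t-test power too high

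*Protocol article*

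**What the plan says.** **Delivery.** The protocol article describes six weekly two-hour sessions under Intervention description {11a}: "The intervention will be conducted in groups of two to six participants per group". The content includes exchange of experiences and joint discussion, and one nurse leads every session. Under Explanation for the choice of comparators {6b}, usual care on sleep is occasional, informal conversation in the clinic, with no therapy groups.

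**Analysis.** Statistical methods {20a} states that "observations on different patients will be assumed to be independent". The mixed model is specified "with participants as the random effect factor". The article calls the model multilevel, but the levels are visits within participants. There is no term for therapy group. The sensitivity analyses under {20c} concern missing data and the per-protocol set.

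**Sample size {14}.** The calculation is an unclustered comparison of two means at the two-sided 5% level, "assuming a common standard deviation of 7.5% in SE". With 30 patients in each arm, the article reports that the design "has a power of 86.1% to detect a mean difference of 6 percentage points in SE". After up to four withdrawals per group (52 patients) the stated power is 80.7%, presented as above 80%. No ICC or design effect appears.

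**The concern.** Patients treated together share sessions, discussion, timing and group dynamics. These are the usual reasons to expect outcomes within a therapy group to be more alike than outcomes across groups. Only the CBT-i arm has such groups, so the design is partially nested. The independence assumption is stated outright, so this is not a detail left to a later analysis plan.

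If the ICC is positive, the variance of the CBT-i mean is larger than the model believes. The interval for the treatment difference is then too narrow and the nominal test levels are exceeded. The section also undertakes to hold the type I error at 5% through a hierarchy, and the primary test at week 7 opens the testing of all secondary outcomes. The stated 80.7% has only 0.7 points to spare above 80%.

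**Working it through.** **Inputs from the protocol.** Difference 6 points and SD 7.5 points (standardised 6/7.5 = 0.8); two-sided 5%; n = 30 per arm, or 26 after attrition; group size m from 2 to 6, that is 30/6 = 5 to 30/2 = 15 therapy groups.

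**Assumed.** ICC from 0.01 to 0.10, because the protocol gives none.

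**Step 1: reproduce the stated power (independence).** SE = 7.5 × √(2/n).
- n = 30: SE = 1.936, noncentrality 6/1.936 = 3.098, 58 df, power 86.1%.
- n = 26: SE = 2.080, noncentrality 2.884, 50 df, power 80.7%.

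Both stated figures reproduce, so the arithmetic is right under independence.

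**Step 2: cluster the CBT-i arm only.** The design effect in that arm is DE = 1 + (m − 1) × ICC, and SE = 7.5 × √((1 + DE)/n). The ratio of true to planned SE is √((1 + DE)/2). For m = 5 and ICC 0.05, DE = 1.20 and the ratio is √1.10 = 1.049. Over the whole grid the true SE exceeds the planned one by 0.2% (m = 2, ICC 0.01) to 11.8% (m = 6, ICC 0.10).

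**Step 3: power on the protocol's own t-test basis**, degrees of freedom unchanged, shown as 60 patients / 52 patients:

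| m | ICC 0.01 | ICC 0.02 | ICC 0.05 | ICC 0.10 |
|---|---|---|---|---|
| 2 | 86.0 / 80.6 | 85.8 / 80.4 | 85.3 / 79.8 | 84.5 / 78.8 |
| 4 | 85.6 / 80.2 | 85.1 / 79.6 | 83.6 / 77.9 | 81.1 / 75.1 |
| 5 | 85.5 / 80.0 | 84.8 / 79.2 | 82.8 / 76.9 | 79.4 / 73.3 |
| 6 | 85.3 / 79.8 | 84.5 / 78.8 | 81.9 / 76.0 | 77.8 / 71.6 |

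For 52 patients, power falls below 80% at an ICC of 0.02 once groups have four or more members.

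**Step 4: degrees of freedom.** A Satterthwaite correction, with (number of groups − 1) df in the CBT-i arm, lowers power further. For 60 patients at ICC 0.05 it is 78.8% (m = 5) and 76.4% (m = 6).

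**Step 5: error of the unadjusted test.** This was simulated with 30 per arm, zero mean difference and groups of five. The nominal 5% test rejects in about 5.4%, 6.2% and 7.4% of trials at ICC 0.02, 0.05 and 0.10; separate simulations put the middle figure between 6.1% and 6.3%. With groups of six, ICC 0.10 gives 8.0%. For the key secondary thresholds, with groups of five and ICC 0.10, a nominal 0.01 becomes about 1.8% to 1.9% and a nominal 0.017 about 2.8% to 2.9%.

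**The case against.** **The ICC is unknown and may be small for the primary outcome.** Sleep efficiency comes from home polysomnography scored by blinded staff, not from self-report. One nurse leads all sessions from a manual, so therapists do not vary, and missed sessions are made up individually. This stands as a reason for caution about size. It does not justify fixing the ICC at zero, and five of the eight key secondary outcomes are patient-reported.

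**If therapy did nothing for anyone, shared sessions could create no correlation.** Type I inflation then needs group effects that average to zero, or correlation from how groups are formed. This stands for the strict null. It does not rescue the interval when therapy works better in some groups than in others.

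**The power figures ignore baseline adjustment.** A reader might infer that 86.1% and 80.7% are upper bounds on the trial's power. They are not: they are unadjusted t-test figures, and the planned model includes baseline. Suppose 7.5 is the unadjusted SD, the baseline correlation is r (not given), and the variance of the difference is 7.5² × [2(1 − r²) + (m − 1) × ICC]/n. With groups of five and ICC 0.05, power for 60 patients is then 85.8% at r = 0.3 and 91.0% at r = 0.5; for 52 patients it is 80.3% and 86.6%. The gain can offset the loss in power, before any loss of degrees of freedom. It does not make the standard error correct.

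**Group size may be smaller than five**, especially after attrition: 26 patients in six groups average 26/6 = 4.33. That is why the table spans two to six.

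**The remedy is not effortless.** With six groups of five, an ANOVA-type estimate of the group variance is zero or negative in about 51%, 43% and 33% of trials at ICC 0.02, 0.05 and 0.10. A default fit that truncates at zero would then often apply no correction. This stands and shapes the fix.

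**Conclusion.** The independence assumption conflicts with the protocol's own description of delivery and should be replaced. The direction is firm for any positive ICC; the size rests on an assumed ICC of 0.01 to 0.10. On the t-test basis the stated power is too high by between about 0.1 and 8.3 points at 60 patients (86.1 − 86.0; 86.1 − 77.8) and between about 0.1 and 9.1 points at 52 (80.7 − 80.6; 80.7 − 71.6). With groups of two or an ICC near 0.01 the loss at 60 patients is under 1 point, except for groups of two at ICC 0.10, where it is 86.1 − 84.5 = 1.6 points.

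Stronger readings are not supported:
- That the interval is certainly too narrow. This depends on an ICC that the protocol does not give.
- That error rises above 5% for every outcome. The key secondary outcomes are tested at 0.01 and 0.017; each may exceed its own level but stays below 5% in these calculations.
- That the full design effect applies to all 60 patients. Controls are not clustered, so this would overstate the loss.

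Severity: should be fixed.

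**What to change.** 1. Replace the independence sentence: patients are independent across therapy groups and in the control arm, while patients in the same CBT-i group may be correlated.
2. Record a therapy-group identifier for every CBT-i participant.
3. Fit a partially nested mixed model: a therapy-group random effect in the CBT-i arm only, controls as singletons, with Kenward-Roger or Satterthwaite degrees of freedom. Keep the group term whatever its estimate, and do not truncate its variance at zero (for example, NOBOUND in PROC MIXED).
4. Report the ICC with its interval.
5. Restate power as a range over ICC and group size, with the sample size unchanged.

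**Cost.** One extra variable and a modest change to the model code. Intervals will be slightly wider, degrees of freedom fewer and the stated power less favourable. The ICC will be imprecise with only about 5 to 15 groups, which is a reason to fix the model before the outcome data are examined.
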